### Data Collection

#### Phase 1

After recruitment and enrollment into the study (week 1), nursing students in each semester will be randomized into either the intervention or control group and will be assigned a unique participant code number. The allocation ratio will be 1:1 (intervention or control group), following a simple randomization procedure (Microsoft Excel [Microsoft Corp.] random number table). Research team members involved in data collection will be blinded to the allocation; participants will become aware of their randomization on receipt of an email from the researchers outlining their allocation into the intervention or control group. At this time, students in the intervention group will receive access to the eMAR simulation game approximately 2 weeks in advance of their in-person simulation sessions with the eMAR technology in the CSL. Along with access to the eMAR simulation game, students in the intervention group will also have access to other usual preparatory educational resources related to medication administration, such as a video demonstrating proper administration technique and a PowerPoint presentation on eMAR medication administration. To ensure a consistent duration of game intervention, students will be requested to use the eMAR simulation game for a minimum of 60 min (with no maximum) [29] before conducting their return demonstration of a medication administration using the actual SMART eMAR system in the CSL (starting week 5); analytics software operating in the background of the game will be used to track the average game play duration of participants. Students allocated to the control group will receive the usual preparatory resources related to eMAR medication administration, without access to the eMAR simulation game. At the conclusion of the trial in late October and February (week 9), all participants in the control group will receive access to the eMAR simulation game.

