The duration of the active trial in each academic semester will be approximately 4 weeks, running the months of October and February. The simulated return-demonstration patient scenario that all students will be required to complete involves conducting a baseline physical assessment on a high-fidelity human mannequin simulator, performing the ordered medication administration using the SMART eMAR system, and conducting a patient follow-up assessment and documentation of the encounter in the patient’s clinical record. All participants in the intervention and control groups will receive the same patient and medication administration scenario to maximize contextual internal validity.

Prepost data related to medication self-efficacy and knowledge will be collected through a Qualtrics (Qualtrics Inc.) Web-based survey platform before (week 4) and after the simulated return-demonstration patient scenario (week 8). Cross-sectional survey data will be collected from the intervention group only, immediately after the simulated return-demonstration patient scenario (week 8; Figure 2).

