#### Outcomes

Data will be collected by 4 data collectors (nursing graduate students with clinical backgrounds using eMAR technology) who will observe nursing student participants during their return demonstration of medication administration using the SMART eMAR (weeks 5-8). These data collectors will be trained by members of the research team before the study initiation to ensure the appropriate and consistent use of the checklist to collect participant data. Mock student return demonstrations and related data collection will be conducted to improve interrater reliability; Fleiss kappa coefficients will be calculated and used to further refine interrater reliability of the data collection procedure. A formalized checklist that has been developed and used previously in an adapted form by the research team [20] will be implemented as the primary data collection instrument for phase 1. This data collection checklist will capture the following quantitative data during each participant’s medication administration return demonstration using the SMART eMAR: (1) frequency of deviations from medication administration best practices, (2) number of actual medication errors or near misses generated by the student that violate the various medication best practices and provincial regulatory requirements related to medication administration [30,31], and (3) overall duration of time required by the student to complete the entire medication administration simulated scenario. Secondary outcomes using prepost survey data related to medication self-efficacy and knowledge will be collected using questions modified from previously developed and tested instruments [32,33]. Secondary outcome cross-sectional data will also be collected using questions modified from the Huang et al’s [34] validated instrument that measures motivational (ie, attention, relevance, confidence, satisfaction) and cognitive processing of learning in game-based environments (20 questions, Cronbach alpha=.91). Measurement of motivational and cognitive processes of learning will identify levels of participant motivation related to cognitive load requirements demanded by the eMAR simulation game.

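### The week-4 survey is not a clean pre-intervention baseline for self-efficacy and knowledge, because game access and the allocation email come at about week 3 for at least the earliest-session students

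*Protocol article*

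**What the plan says.** All timing statements are in the protocol article.

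- **Allocation** (Data Collection, Phase 1): "After recruitment and enrollment into the study (week 1), nursing students in each semester will be randomized". The exact week is not given, but "participants will become aware of their randomization on receipt of an email from the researchers", and the text ties game access to that moment.
- **Game access** (same section): "students in the intervention group will receive access to the eMAR simulation game approximately 2 weeks in advance of their in-person simulation sessions".
- **Sessions**: the return demonstration is done "using the actual SMART eMAR system in the CSL (starting week 5", and Outcomes has students observed "during their return demonstration of medication administration using the SMART eMAR (weeks 5-8".
- **Amount of play**: "students will be requested to use the eMAR simulation game for a minimum of 60 min (with no maximum", to be done before the return demonstration.
- **Surveys** (Data Collection, Phase 1): "before (week 4) and after the simulated return-demonstration patient scenario (week 8". No earlier survey is described.
- **Status of these data** (Outcomes): "Secondary outcomes using prepost survey data related to medication self-efficacy and knowledge will be collected".

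Research question 2 (Objectives of the Study) asks whether the game improves self-efficacy and knowledge. Data Analysis, Phase 1 promises descriptive and inferential statistics for the survey data. The t test it describes is worded as pre versus post, but the variables listed with it are errors or near misses, deviations and time.

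**The concern.** The two surveys are placed around the return demonstration, which both arms complete. The game, which is what differs between the arms, starts earlier. A score taken after an intervention student has had the game, and after that student knows the allocation, may already carry part of the effect that research question 2 asks about. Subtracting that score, or adjusting for it as a baseline, takes that part out of the estimate and pulls it toward no effect. A null result on question 2 would then be hard to read. Knowing one's arm could also move self-rated confidence by week 4, though the document gives no basis for the direction or size of such a shift.

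**Working it through.** The plan gives no figure to reproduce here. The check is on the order of events and on what that order does to the estimate.

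**1. Order of events.** Access week = session week − 2. Sessions run in weeks 5 to 8 and the first survey is in week 4.

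| Session week | Access, one opening for all | Access, staggered by session | Week-4 survey relative to staggered access |
|---|---|---|---|
| 5 | about 3 | about 3 | about 1 week after |
| 6 | about 3 | about 4 | same week |
| 7 | about 3 | about 5 | before |
| 8 | about 3 | about 6 | before |

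The document does not say outright which pattern applies. Because access is tied to the allocation email, a single opening is the more natural reading. Under either pattern, week-5 students complete the first survey after access.

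**2. Effect on the estimate.** Let D be the true between-arm difference at week 8, f the average share of D already present in the intervention arm at week 4, and ρ the within-arm correlation of the two scores, with equal SDs. Then:

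- week-8 difference: D
- change-score difference: D − fD = D(1 − f)
- week-8 difference adjusted for the week-4 score: about D − ρfD = D(1 − ρf)

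Both f and ρ are assumed. The share of D that remains is:

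| f | Change score | Adjusted, ρ = 0.5 | Adjusted, ρ = 0.7 |
|---|---|---|---|
| 0 | 100% | 100% | 100% |
| 0.25 | 75% | 87.5% | 82.5% |
| 0.5 | 50% | 75% | 65% |
| 0.75 | 25% | 62.5% | 47.5% |
| 1 | 0% | 50% | 30% |

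**3. Where f might lie.** Suppose the effect builds evenly with play from access until the student's own session, and sessions are spread evenly over weeks 5 to 8. Both are assumptions made for illustration.

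- One opening at week 3: a student with a session in week w has reached (4 − 3)/(w − 3) by week 4, which is 1/2, 1/3, 1/4 and 1/5. The mean is 1.283/4 = 0.32.
- Staggered access: week-5 students have reached 1/2 and the others 0. The mean is 0.5/4 = 0.125.

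The change score would then keep about 68% or 87.5% of D. Faster early play raises f; later play lowers it.

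**4. Power, as an illustration.** Take 60 per arm (the planned 120 split 1:1), an assumed D of 0.5 SD, a two-sided .05 test and ρ = 0.5, so that the SD of change is √(2(1 − 0.5)) = 1.

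| f | Change-score contrast (SD) | Power |
|---|---|---|
| 0 | 0.50 | 0.775 |
| 0.25 | 0.375 | 0.53 |
| 0.5 | 0.25 | 0.27 |
| 0.75 | 0.125 | 0.10 |

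A simulation of 4,000 trials at D = 0.5 and f = 0.5 gave a mean change-score contrast of 0.247 and a mean week-8 contrast of 0.497. The change score loses the share f; the week-8 comparison does not.

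**The case against.** The strongest reply has five parts.

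- **Week 3 is inferred.** It comes from an approximate lead time and a start week, and Figure 2, which might settle it, is not shown. This stands as a limit on certainty. The stated active period of about 4 weeks also looks too short for access at week 3 and a survey at week 8. However, it matches the four session weeks 5 to 8, so it does not contradict access opening earlier. No date in the text puts the survey ahead of access for week-5 students.
- **No biased analysis is fixed.** A reader might infer that the protocol commits to a change score for the surveys. It does not: the t test is listed with the checklist outcomes, and the survey estimator may be left to a document not shown. This stands. The label pre-post nonetheless points toward a change analysis, and the surveys are the only data described as collected twice.
- **Play continues after week 4.** A reader might infer that weeks 4 to 8 measure only the in-person simulation. The text does not support that. Play has no upper limit and is requested before each student's own demonstration, so later play still adds to the between-arm difference. What both arms gain equally from the simulation cancels.
- **f is unconstrained.** This is correct. The tables show what would happen at each value, not what will happen. The extreme f = 1 would require that no play after week 4 adds anything.
- **The outcomes are secondary and the bias runs toward no effect.** This is also correct. The checklist outcomes are observed during the demonstration and do not use this survey.

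**Conclusion.** The point holds in limited form and should be fixed. For the whole intervention arm under a single opening, or clearly for the week-5 students under staggered access, the first survey comes after access and after allocation is known. It therefore cannot serve as a pre-intervention baseline for the arm as a whole. A change from week 4 would keep 1 − f of the game effect and adjustment about 1 − ρf, with f and ρ unknown. The illustrative build-up patterns give a loss for change scores of 12.5% to 32%, and larger losses are possible.

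It would go too far to say that research question 2 cannot be answered. The arms are randomised, and the between-arm comparison of week-8 scores, available from the data as planned, is not biased by this timing. The primary observational outcomes are unaffected.

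**What to change.** 1. State that the main analysis of self-efficacy and knowledge is the between-arm difference in week-8 scores, in both waves.
2. Describe the week-4 survey as an interim measure. Do not use it as a baseline, either by subtraction or as a covariate.
3. State when game access opens relative to that survey, and whether access is simultaneous or tied to each student's session.
4. Where still feasible in wave 2 (January 2018 start), send the web survey at enrolment, before the allocation email and game access. Adjust only for scores taken at that point.

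**Cost.** Items 1 to 3 are wording changes. Item 4 moves one web survey about 3 weeks earlier. According to Results, data collection for the fall cohort has concluded, so wave 1 gives up the precision of baseline adjustment. With an assumed ρ of 0.5 to 0.7, a clean baseline would have cut the variance to 1 − ρ² = 0.75 to 0.51 of the unadjusted value. The two waves would also have pre-measures taken at different times, which is why baseline adjustment should stay within wave 2. If wave 2 is too far advanced for item 4, items 1 to 3 still remove the bias.

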### Objectives of the Study

The main objectives of this study are to examine whether the use of an eMAR simulation serious game (1) improves nursing students’ attention to medication administration safety within simulated practice, (2) increases student self-efficacy and knowledge of the medication administration process, and (3) improves motivational (ie, attention, relevance, confidence, and satisfaction) and cognitive processing attributes (ie, invested mental effort and difficulty to learn game) related to student learning in a technology-enabled environment. Three specific research questions will be addressed in this study:

Does the use of an eMAR simulation game improve the eMAR medication administration safety for nursing students during in-person, simulated clinical practice?Does the use of an eMAR simulation game improve learner self-efficacy and knowledge toward eMAR medication administration processes in nursing students for in-person, simulated clinical practice?Does the use of an eMAR simulation game improve the motivational and cognitive processing attributes of nursing students regarding their learning of eMAR medication administration in a technology-enabled environment?

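### Objective 3 and research question 3 ask whether the game improves motivation and cognitive processing, but these are measured once, in the game arm only, so the survey can describe but cannot show improvement

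*Protocol article*

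**What the plan says.** The Abstract and Objectives of the Study in the Protocol article list three objectives. The third is whether the game "improves motivational (ie, attention, relevance, confidence, and satisfaction) and cognitive processing attributes". Research question 3 repeats the verb: "Does the use of an eMAR simulation game improve the motivational and cognitive processing attributes of nursing students".

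Outcomes assigns one 20-question instrument to these attributes and introduces it with the words "Secondary outcome cross-sectional data will also be collected using questions modified from" a validated game-based learning questionnaire. No other measure in the article is called cross-sectional. The same section says what the measurement is for: it "will identify levels of participant motivation related to cognitive load requirements demanded by the eMAR simulation game".

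Data Collection (Phase 1) fixes who is surveyed and when: "Cross-sectional survey data will be collected from the intervention group only, immediately after the simulated return-demonstration patient scenario", in week 8. The sentence before it reserves repeated measurement for other outcomes: "Prepost data related to medication self-efficacy and knowledge will be collected". Control students prepare with the usual resources "without access to the eMAR simulation game" and receive the game in week 9.

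Data Analysis (Phase 1) says in general terms that survey data will be analysed descriptively and inferentially. It names t tests only for errors or near misses, deviations and time.

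**The concern.** To say that the game improves an attribute is a causal claim. It needs a comparator: the same students before exposure, or the randomised students without the game. The plan has neither for this outcome. Randomisation does not help, because the control arm is never measured on the instrument.

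One of the three numbered objectives, repeated in the Abstract, therefore cannot be answered as worded. If the wording stays, a favourable score among game users could be taken as a randomised effect when it is an uncontrolled single-arm description.

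**Working it through.** **1. Trace research question 3 to its data.** The article gives no figure to reproduce for this outcome, so the check sets the passages side by side.

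| Element | Where stated | Content |
|---|---|---|
| Question | Objectives of the Study | Does the game improve motivational and cognitive processing attributes? |
| Instrument | Outcomes | One 20-question instrument, cross-sectional |
| Arm | Data Collection | Intervention only |
| Time points | Data Collection | One, week 8 |
| Baseline | Data Collection | Self-efficacy and knowledge only |
| Stated yield | Outcomes | Levels of motivation in relation to cognitive load |
| Named comparison | Data Analysis | None for these attributes |

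The Data Collection sentence does not name the instrument. The link comes from Outcomes, where this is the only cross-sectional measure.

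**2. What can be estimated.**
- Change within students = mean(post) − mean(pre), game arm. The second term is never collected.
- Difference between arms = mean(game) − mean(control). The second term is never collected.
- Level among game users = mean(game, week 8). Available.
- Association of motivation with cognitive load among game users, week 8. Available.

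The first two fail for lack of data, not lack of power.

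**3. Precision of what remains.** Assume 120 recruited (Setting and Recruitment of Participants), an even 1:1 split and full response, giving 120 / 2 = 60 game users.
- Mean: half-width in SD units = t(0.975, n − 1) / √n = 2.00 / 7.75 = 0.26.
- Range: if 80% of the 60 respond (assumed), n = 48 and 2.01 / 6.93 = 0.29. If all 150 eligible students took part and responded, n = 75 and 1.99 / 8.66 = 0.23.
- Correlation: half-width on the Fisher z scale = 1.96 / √(60 − 3) = 1.96 / 7.55 = 0.26, or about ±0.25 for a correlation near zero.

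Simple randomisation does not fix arm sizes, so 60 is approximate.

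**4. What a late control survey could add.** The Results section says fall 2017 collection has concluded, so control data could come only from wave 2. Assume 120 participants split evenly over two waves and two arms: 120 / 4 = 30 per arm. The smallest standardised difference d with 80% power in a two-sample, 2-sided t test at .05 is:

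| Per arm | Assumption | d |
|---|---|---|
| 24 | 80% of 30 respond | 0.83 |
| 30 | 120 split evenly | 0.74 |
| 37 | all 75 students in the semester take part | 0.66 |

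**The case against.** **It is a secondary outcome.** This stands. The observed checklist (deviations, errors or near misses, time) covers both randomised arms, and the self-efficacy and knowledge outcomes do not depend on this questionnaire. A reader might infer that the trial's main comparison is undermined; nothing in the document supports that.

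**One-arm collection has a reason.** This also stands. The instrument concerns game-based learning, one listed attribute is how hard the game is to learn, and control students have no game until week 9. It would be wrong to call the one-arm survey an oversight. The reason explains the collection, however, and does not support the verb in the objective.

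**The operational text is already descriptive.** Largely true. The data are labelled cross-sectional, the restriction to one arm is stated openly, and the purpose given is to identify levels. A reader might infer that the authors plan to report this survey as a randomised effect. The document does not say so; the overreach is in the Abstract, the objective and the question.

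**More than a mean can be estimated.** Correct. A reader might infer that a mean level is the only usable result, but Outcomes also points to motivation in relation to cognitive load, which can be examined within the game arm.

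**The article is condensed and other material may fill the gap.** This does not stand. The article states one arm and one time point, and no analysis plan can create the missing values. The focus groups include both arms, but they are qualitative, involve about 20 students and do not measure change on this instrument. Figure 2 is not shown, but the text is explicit.

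**Conclusion.** The mismatch holds. As designed, the survey gives no causal estimate, no between-arm estimate and no estimate of change for objective 3, at any sample size. It can describe levels of motivation and cognitive load among game users, and their association. The precision figure of about 0.26 SD (0.23 to 0.29 over the range shown) rests on assumed numbers of responders; the main conclusion rests on no numerical assumption. The problem is confined to one secondary outcome and to the claim attached to it, but the wording should be corrected before results are reported, because later analysis cannot repair it.

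**What to change.** **Main change: wording.** In the Abstract and Objectives of the Study, restate objective 3 and research question 3 as describing the levels of motivation and cognitive load, and the relation between them, among students who used the game. Report means with 95% confidence intervals and the association with its interval. Drop *improve*, and state that no conclusion on effectiveness will be drawn from this survey. This needs no new data and adds no burden for students.

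**Optional, exploratory only.** If wave 2 collection is still open, give neutrally worded items that do not depend on the game to both arms after the return demonstration and before controls get access in week 9. Keep the item on difficulty of learning the game in the intervention arm. The cost is at most 20 extra web questions for wave 2 controls, with limits that should be stated:
- About 30 per arm (assumed), with 80% power only for d of about 0.74.
- No pooling with wave 1, whose game users answered the game-based version.
- The reworded items do not inherit the cited instrument's validation or its alpha of .91.
- Game-arm students also receive the video and PowerPoint, so a question about preparation materials refers to a different bundle in each arm, and students know their allocation.

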#### Outcomes

Data will be collected by 4 data collectors (nursing graduate students with clinical backgrounds using eMAR technology) who will observe nursing student participants during their return demonstration of medication administration using the SMART eMAR (weeks 5-8). These data collectors will be trained by members of the research team before the study initiation to ensure the appropriate and consistent use of the checklist to collect participant data. Mock student return demonstrations and related data collection will be conducted to improve interrater reliability; Fleiss kappa coefficients will be calculated and used to further refine interrater reliability of the data collection procedure. A formalized checklist that has been developed and used previously in an adapted form by the research team [20] will be implemented as the primary data collection instrument for phase 1. This data collection checklist will capture the following quantitative data during each participant’s medication administration return demonstration using the SMART eMAR: (1) frequency of deviations from medication administration best practices, (2) number of actual medication errors or near misses generated by the student that violate the various medication best practices and provincial regulatory requirements related to medication administration [30,31], and (3) overall duration of time required by the student to complete the entire medication administration simulated scenario. Secondary outcomes using prepost survey data related to medication self-efficacy and knowledge will be collected using questions modified from previously developed and tested instruments [32,33]. Secondary outcome cross-sectional data will also be collected using questions modified from the Huang et al’s [34] validated instrument that measures motivational (ie, attention, relevance, confidence, satisfaction) and cognitive processing of learning in game-based environments (20 questions, Cronbach alpha=.91). Measurement of motivational and cognitive processes of learning will identify levels of participant motivation related to cognitive load requirements demanded by the eMAR simulation game.

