**Figure 1 figure1:**
[figure not shown]
Screenshot of the electronic medication administration record (eMAR) simulation game’s user interface and various player-manipulable objects.

Before the start of each term, a researcher-led presentation will be delivered outlining the proposed study purpose, methods, and study benefits. Given the typical student enrollment within second year of the BScN program, it is expected that approximately 150 students will fit this inclusion criterion and be eligible for recruitment into the study. Participants will be offered a Can $5 gift card for a coffee shop as a nominal incentive to participate in the study. Due to the high recruitment success rate experienced in the corresponding pilot study completed in April 2016 (25/27, 93% of students sampled) [11], we estimate 120 participants will be recruited. By including at least 120 participants, phase 1 of our study will be able to detect an intervention effect size of 0.25, with a power of 0.8 and a .05 level of significance, based on a 2-tailed *t* test analysis, as calculated by G*Power 3.1 (Heinrich-Heine-Universität Düsseldorf, Germany).

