### Data Analysis

#### Phase 1

Survey data will be analyzed through descriptive and inferential statistics. Student *t* test to compare pre- versus postcontinuous outcomes for intervention and control groups in relation to number of medication errors or near misses, number of deviation from best practices, and length of time (efficiency) of administration will be completed.

#### Phase 2

Semistructured focus group interviews will be audio recorded and transcribed verbatim. A minimum of 2 researchers will conduct a directed content analysis [36] of the data; this will be triangulated with quantitative findings [37] to generate a deeper understanding of the effectiveness of the gamified eMAR simulation as a technology-enabled clinical education tool.

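### No single primary outcome is named among the three checklist measures, and the one .05 power statement is tied to none of them, so the two safety measures together carry more than the stated error.

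*Protocol article*

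**What the plan says.** The Outcomes section of the protocol article describes an observer checklist that yields three measures per student. The first two are "1) frequency of deviations from medication administration best practices, (2) number of actual medication errors or near misses generated by the student", and the third is the time needed to complete the scenario. In that section the word primary is attached to the checklist as an instrument, not to any one measure. The survey measures (self-efficacy, knowledge, motivation and cognitive processing) are labelled secondary. The three checklist measures are therefore primary only by implication, as a group and in no order.

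Errors or near misses are further described as those "that violate the various medication best practices and provincial regulatory requirements related to medication administration".

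Data Analysis, Phase 1, plans a Student t test for the number of errors or near misses and also for "number of deviation from best practices, and length of time (efficiency) of administration will be completed". Time is thus described as a measure of efficiency.

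The sample-size statement, under Setting and Recruitment of Participants, claims that "phase 1 of our study will be able to detect an intervention effect size of 0.25". The calculation takes a total of 120 students and a two-sided t test, and its error rates are given by the words "with a power of 0.8 and a .05 level of significance". It does not say which measure the effect size refers to. No significance level is stated anywhere else.

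**The concern.** Research question 1 asks whether the game improves medication administration safety. Two of the three checklist measures bear on that directly. The article gives no order between them and no rule for what counts as success. A difference on either could be offered as the answer, and nothing says what follows if the arms differ on one and not the other.

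Two things are at stake. The first is the error rate of the main claim: .05 for one test is not .05 for a claim that either of two tests may support. The second is freedom of choice after the data are seen. The Results section reports that collection for the fall 2017 cohort has finished and that preliminary results on half the cohort are expected ahead of the full findings. A headline measure chosen after those results would be data-driven.

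The power statement shares the gap. It cannot be checked against a standard deviation or a meaningful difference, because it is not attached to a measure.

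**Working it through.** **Inputs.** From the article: total sample 120; "The allocation ratio will be 1:1 (intervention or control group"), so about 60 per arm; one two-tailed level of .05; power 0.8; effect size 0.25, metric not named; three checklist t tests. Not in the article, hence assumed: that each test is run at .05, and the correlation between measures, taken from 0 to 0.9.

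**The plan's own figure.** I used noncentral t power, two-sided .05.
- Cohen's d = 0.25, independent groups: 253 per arm needed; power with 60 per arm is 27%.
- d = 0.5, independent groups: 64 per arm needed; power with 60 per arm is 77.5%.
- 0.25 as a point-biserial correlation: noncentrality √(N·r²/(1−r²)) with N − 2 degrees of freedom gives 79.8% at N = 119 and 80.1% at N = 120.

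Only the last reading reproduces 120. It corresponds to d = 2(0.25)/√(1 − 0.0625) = 0.52. The stated numbers thus describe one test at .05, with no allowance for a second or third.

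**Chance of at least one false-positive result, no true effect on any measure.**

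For independent tests the formula is 1 − (1 − α)^k.
- Three measures, either direction: 1 − 0.95³ = 14.3%.
- Two safety measures, either direction: 1 − 0.95² = 9.75%.
- Three measures, in the game's favour: 1 − 0.975³ = 7.3%.
- Two safety measures, in the game's favour: 1 − 0.975² = 4.9%.

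For correlated tests I used 1,000,000 draws of correlated normal test statistics with critical value 1.96.

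| Common correlation (assumed) | Three, either direction | Two safety, either direction | Three, in favour | Two safety, in favour |
|---|---|---|---|---|
| 0 | 14.3% | 9.75% | 7.3% | 4.9% |
| 0.5 | 12.6% | 9.1% | 6.3% | 4.5% |
| 0.7 | 10.9% | 8.3% | 5.4% | 4.2% |
| 0.8 | 9.8% | 7.8% | 4.9% | 3.9% |
| 0.9 | 8.4% | 7.1% | 4.2% | 3.5% |
| One named primary | 5% | 5% | 2.5% | 2.5% |

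For correlations from 0.7 to 0, the error over the two safety measures is 8.3/5 = 1.7 to 9.75/5 = 1.95 times that of a single test. In the game's favour the ratios are 4.2/2.5 = 1.7 to 4.9/2.5 = 2.0.

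**Cost of keeping all three co-primary.** At .05/3 each, with 60 per arm and 80% power, the detectable d rises from 0.52 to 0.60.

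**The case against.** The strongest case against is that a condensed article commonly leaves multiplicity to an analysis plan, which is not shown here, and that .05 appears only in the sample-size statement. That stands as far as it goes: the absence of an adjustment method is not the finding, and testing each measure at .05 is an assumption. It does not reach the main point. Naming the primary outcome, and the outcome that the sample size serves, belongs in the protocol. This article has an Outcomes section that labels other measures secondary, and it still does not do so.

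Three stronger readings are tempting, and the document does not support them.

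- A reader might infer that 11–14% is the chance of falsely claiming that the game improves safety. That range counts significant results in both directions, including those where the game looks harmful. It also counts time, which the article treats as efficiency. For a claim of improved safety the range is 4.2–4.9%, and the comparator is 2.5%, not 5%.
- A reader might infer that all three measures overlap. Only errors or near misses and deviations may do so, because the former are described through violations of best practices. Nothing in the definitions links time to either.
- A reader might infer that every error is also scored as a deviation. The description of errors refers to regulatory requirements as well as best practices, and the checklist's scoring rules are not shown. Double counting is possible but not established.

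It can also be said that possible overlap makes independence unlikely for the two safety measures, so the upper ends of the ranges are generous. That is fair. Even at a correlation of 0.9, however, the two-measure error is about 7.1% against 5%.

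**Conclusion.** The point holds in moderate form. The article names no single primary outcome among three separately tested measures and ties its one power statement to none of them. Over the two safety measures, the chance of at least one false-positive result is 8.3–9.75% in either direction against 5%, and 4.2–4.9% in the game's favour against 2.5%. Over all three measures it is about 11–14% in either direction.

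These figures rest on testing each measure two-sided at .05 and on assumed correlations from 0.7 to 0. Higher correlation shrinks the inflation without removing it. The larger practical risk is that the headline measure could be picked once results from the first wave are known. The plan should be corrected, but the defect does not by itself invalidate the trial.

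**What to change.** Name one safety measure as the single primary outcome, tested at .05, and tie the sample-size statement to it. The number of medication errors or near misses is one candidate. Which safety measure best answers research question 1 is a judgement for the investigators, since objective 1 speaks of attention to safety and deviations could also serve it. When restating the power, say which metric the 0.25 is in.

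Make the other safety measure and time secondary, either tested with Holm's procedure or reported as estimates with confidence intervals.

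Record the choice before anyone sees between-arm results from either wave. If that is no longer possible, disclose the date of the choice and what had been seen by then. State how the existing checklist scores an event that could fall under both safety measures, but do not redefine or rescore the deviation count mid-trial.

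The change is one of wording and needs no further participants or visits. Its downside is that a significant result on a secondary measure alone would no longer support the main claim.
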